#### Short - Falls Efficacy Scale – International (Short-FES-I):

Fall-related self-efficacy will be registered using the 7-item Short-FES-I [44], measuring the level of concern about falling during indoor/outdoor social and physical activities. A total score of 7 (no concern about falling) to 28 (severe concern about falling) can be achieved.

#### Fear of Falling Avoidance Behavior Questionnaire (FFABQ):

The FFABQ is used to assess activity avoidance behavior due to fear of falling [45]. The FFABQ total score ranges from 0 to 56 points. Higher score indicate greater activity limitations and participation restrictions as a consequence of fear of the falling.

#### Cognitive Performance

The Digit-Span sub-test of the Wechsler Adult Intelligence Scale (WAIS) [46] is registered to assess participants’ short-term working memory. The number of correct repetitions is used for further analyses.

### Cost effectiveness

To evaluate cost effectiveness, incremental cost-effectiveness ratios (ICERs) will be calculated [47]. ICERs are calculated by dividing the difference in costs (between the INTV and the CTRL) by the group difference in the outcomes and can be interpreted as the cost to obtain an extra unit of effectiveness, quantifying the trade-offs between patient outcomes gained and resources spend [47]. In our analysis, ICERs will be calculated for primary outcomes (e.g., *motor performance; SPPB total score*) and secondary outcomes (e.g., *health-related quality of life; EQ-5D questionnaire*). Therefore, average costs of the exercise interventions (e.g., training material, visits by trainer, phone calls) as well as overall health care costs (e.g., general practitioner consultations, inpatient and outpatient care, days in hospital, hours of nursing care, hours of professional domestic help or help by family members/friends) will be collected for INTV and CTRL [48]. Overall health care costs will be assessed retrospectively, covering a period of 12 weeks before T1, T2 and T3, using an established questionnaire (FIMA) [49].

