### Psycho-social parameters

#### Health-related quality of life – EuroQol - 5 Dimensions (EQ-5D):

The EQ-5D, including five health-related domains (mobility, self-care, pain/discomfort, usual activities and anxiety/depression) will be used to measure health-related quality of life [38]. Outcome parameters are the EQ-5D total score (5–15 points) and participants’ self-rated perceived health status (0–100 points).

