### Intervention

Participants in INTV take part in a standardized 12-week home-based training program. The program is specifically-tailored for geriatric patients with CI after post-ward rehabilitation to improve motor performance and enhance PA. The training intervention was derived from an exercise program developed by our research group, which was feasible and effective to increase strength and functional performances in patients with CI [24]. Based on results of a successfully conducted home-based exercise pilot RCT, our program includes six exercises to improve static and dynamic postural control (i.e., standing and walking) and strength (i.e., tiptoe stance, stair climbing, sit-to-stand transfers). Exercises are explained and regularly reviewed by a professional trainer and illustrated at the patient’s home using a large poster (84.1 × 59.4 cm; Fig. 2). A brief description of key elements for each exercise is provided using a printed manual. Training progress and adherence is supervised by weekly phone calls and regular home visits of the trainer (5 visits in 12 weeks).

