The training program will include a motivational concept that is based on the Theory of Planned Behavior (TPB [50]), Social-Cognitive Theory (SCogT [51]), and Control Theory (CT [52]). The concept will use behavioral change techniques introduced by Abraham & Michie (cf. [53] for a detailed description of the theoretical framework) and integrated into our intervention as followed:Information about benefits/consequences of regular training and walking sessions are provided (based on TPB);Encouragement to change daily routines (i.e., integrate training, walk regularly, join a local sport club) (based on TPB);Barrier identification that hamper training and development of solutions to overcome barriers (based on SCogT);Set graded tasks (i.e., variations of exercises and walking trails are developed) (based on SCogT);Provide specific instructions (during home visits using poster and manuals) (based on SCogT);Definition of training goals (i.e., frequency, intensity and duration of exercises and walking trails) (based on CT);Review of behavioral goals (home visits, regular phone calls, pedometer) (based on CT);Self-monitoring of behavior (training logs, pedometer) (based on CT);Provide feedback to reinforce behavioral change (home visits, phone calls, pedometer) (based on CT/positive).

These behavioral change techniques are used to encourage patients to translate their intentions into behavioral change. Participants are expected to develop intrinsic motivation and volition to adapt their behavior.

Participants in CTRL receive newsletter-based information about unspecific flexibility and strength training, nutrition and relaxation over a period of 12 weeks. Similar to INTV, participants are called weekly and receive the same amount of home visits as the INTV group to exclude bias effects based on social support. After finishing the project, participants in CTRL will have the opportunity to perform the same exercise program than INTV and also join the local sports club.

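### The planned ICER nets out trainer visits and calls that the control arm receives only as an attention control, so it understates the delivery cost of adopting the program

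*Protocol article*

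**What the plan says.** The Cost effectiveness section defines the ratio: "ICERs are calculated by dividing the difference in costs (between the INTV and the CTRL) by the group difference in the outcomes". It adds that the result "can be interpreted as the cost to obtain an extra unit of effectiveness". The delivery costs are the "average costs of the exercise interventions (e.g., training material, visits by trainer, phone calls"). Health care use is costed as well, and the section says that all these costs "will be collected for INTV and CTRL".

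The Intervention section says that training in INTV is "supervised by weekly phone calls and regular home visits of the trainer (5 visits in 12 weeks"). Its last paragraph says of CTRL that "participants are called weekly and receive the same amount of home visits as the INTV group to exclude bias effects based on social support".

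The intended use is stated elsewhere. The last paragraph of the Background wants a program that can be taken into existing care. The opening of the Discussion points to its low supervision and material costs. A later Discussion paragraph on financial burden presents the ICER as the means of showing cost effectiveness.

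For quality of life, the Cost effectiveness section names the EQ-5D questionnaire as an example of an ICER outcome without saying which score. The EQ-5D section reads "Outcome parameters are the EQ-5D total score (5–15 points") and adds a 0–100 self-rating of health. The Secondary outcomes list gives the same two scores.

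**The concern.** The control contacts serve the efficacy comparison: they stop trainer attention from being mistaken for an exercise effect. They are not described as part of existing care. When their cost is subtracted from the cost of the INTV contacts, a research device offsets one of the two resources, supervision and materials, that the Discussion itself names when it calls the program inexpensive. The ratio then prices the program relative to an equally visited control group. A payer deciding whether to add the program to present care would have to pay for the visits and calls in full.

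The denominator raises a smaller question. A cost per extra unit of effectiveness presupposes that a higher score is better. The protocol extends ICERs to secondary outcomes without fixing the EQ-5D score or saying how scales that run the other way will be handled.

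**Working it through.** The protocol states no unit cost, cost difference or ICER, so there is no figure of its own to reproduce.

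**Inputs from the protocol**
- INTV: 5 home visits, and weekly calls over 12 weeks, taken as 12 calls (Intervention).
- CTRL: weekly calls and the same number of visits (Intervention, last paragraph).
- Costs in both arms, differenced INTV minus CTRL (Cost effectiveness).

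**Step 1: delivery cost per patient.** Let V be the cost of a visit, C of a call, M of INTV materials and m of the CTRL newsletter.
- INTV: 5V + 12C + M
- CTRL: 5V + 12C + m
- Difference: M − m

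With equal unit costs in both arms, 5V + 12C drops out whatever V and C are. Any difference in health care costs is added to M − m. The Secondary outcomes list mentions an ICER for operational as well as health care costs. If a separate operational ratio is meant, its numerator would be M − m alone.

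**Step 2: size, with assumed unit costs.**

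| V (EUR) | C (EUR) | 5V + 12C (EUR) |
|---|---|---|
| 30 | 5 | 150 + 60 = 210 |
| 50 | 10 | 250 + 120 = 370 |
| 80 | 15 | 400 + 180 = 580 |

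With M assumed at EUR 20 to 100, the share of INTV delivery cost that drops out runs from 210/(210 + 100) = 68% to 580/(580 + 20) = 97%.

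For an assumed gain of 1 SPPB point, the cost per point, read as an adoption cost, is too low by EUR 210 to 580. For 0.5 point it is too low by 210/0.5 = 420 to 580/0.5 = 1,160.

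**Step 3: unequal unit costs.** If a CTRL contact costs a fraction r of an INTV contact, the amount removed is r(5V + 12C). At r = 0.5 this is EUR 105, 185 and 290 for the three rows. The effect shrinks in proportion but does not vanish unless the CTRL contacts are costed at zero.

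**Step 4: the denominator.** Five items at levels 1 to 3 give sums from 5 × 1 = 5 to 5 × 3 = 15. That matches the stated range, so the total score looks like an unweighted sum. Its direction is not stated. The GDS-SF, AES-C, Short-FES-I and FFABQ are each described so that a higher score is worse. If one of them entered the ICER uncoded, an assumed net cost of EUR 300 with a 0.5-point benefit would give 300/(−0.5) = −600 instead of +600.

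**The case against.** The strongest reply is that cost and effect are both measured against the same comparator, so the ratio is a coherent within-trial estimate. That stands. Charging the full program cost against an effect measured over attention control breaks this match and tilts the result against the program, so that costing should not simply replace the planned one.

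Further points on the same side also stand:
- The protocol matches the number of contacts, not their length, content or unit cost. INTV visits include exercise review, goal setting and work on barriers, so exact cancellation is an assumption.
- Hospital days, nursing hours and informal help stay in the numerator and do not cancel by design.
- Every euro amount and every SPPB gain above is assumed.
- Costing perspective, interval methods and similar detail may sit in an analysis plan that is not shown.

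The last point does not dispose of the matter. The article itself fixes the formula, the cost items, the arms and the matched contacts, and together these produce the netting.

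A reader might go further and infer that the cost-effectiveness answer will be wrong, or that the program will look almost free. The documents do not support that. The ratio is right for the contrast it makes, only delivery cost is affected, and nothing shows that trainer contact is the largest cost. Nor does the claim of suitability for existing care rest on the ICER alone: it is first stated as a design aim, then argued from low supervision and material costs.

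A reader might also infer that the ICER uses an EQ-5D sum running in the wrong direction, so that a health gain reads as a saving. The protocol neither names the sum as the denominator nor states its direction, and the 0–100 self-rating is also defined.

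**Conclusion.** The point holds in a limited form. Followed as written, the ICER answers what the program costs relative to an equally visited control group. It does not answer what adding the program to existing care would cost, which is the use that the Background and Discussion have in view. For that question it understates delivery cost by up to 5V + 12C per patient: EUR 210 to 580 under the assumed unit costs if contacts cost the same in both arms, and less if CTRL contacts are cheaper. The direction follows from the protocol once CTRL contacts are costed; the amount does not.

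On the denominator, the supportable statement is that the EQ-5D score is not named and that scoring direction is not fixed for ICER outcomes, several of which are defined as higher being worse. This is secondary and can be corrected by recoding.

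Cost evaluation is a secondary outcome, and neither primary outcome is touched.

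**What to change.** In the Cost effectiveness section:

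1. Keep the as-delivered ICER, and say that it compares the program with an attention control.
2. Pre-specify and report beside it a costing in which the research-only contacts in CTRL are set to zero, while INTV visits, calls and materials are charged in full. State that this is conservative, because full program cost is set against an effect measured over attention control.
3. Name the EQ-5D score for the ICER. A utility index derived from the same five items is preferable to an unweighted sum; the value set should be cited.
4. State that every ICER outcome will be coded so that higher means better.

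The cost is a few sentences and one more scenario in the analysis. Costs are already to be collected by arm and the five EQ-5D items are already recorded, so no new patient data are needed. The price of item 2 is two ratios to explain instead of one.

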### Primary outcomes

*motor performance:* SPPB total score (0–12 points)
*physical activity:* duration of active episodes (i.e., sum of standing and walking)

### Secondary outcomes

*motor performance:* SPPB sub-test scores (0–4 points each), TuG total time, sensor-based parameters during SPPB sub-tests (e.g. CoP displacements, CoP velocity, sit-to-stand and stand-to-sit duration, maximum angular velocities), and qualitative gait parameters (e.g., mean step duration, step regularity, turning velocity)
*physical inactivity:* duration of inactive episodes (i.e., sum of lying and sitting), quantitative gait parameters (i.e., cadence as steps per minute, total number of steps, and number of steps per gait episode)
*life-space:* LSA total score (0–90 points), maximum distance from home and mean walking distances (GPS-based measurements)
*quality of life:* EQ-5D total score (5–15 points), VAS score (0–100 points)
*psychosocial status:* GDS-SF total score (0–15 points), AES-C total score (0–54 points), FES-I total score (7–28 points), FFABQ score (0–56 points)
*falls*: fall history, number of falls during the intervention period
*short-term working memory:* WAIS-IV test performance (0–9 points)
*cost evaluation:* ICER for operational as well as health care costs

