### Sample characteristics

Inclusion criteria are (1) patients admitted to ward-based rehabilitation in a geriatric hospital in Heidelberg, Germany; (2) age ≥ 65 years; (3) mild to moderate CI (Mini-Mental-State-Examination [MMSE]: 17–26); (4) ability to walk 4 m without support; (5) residency within 30 km of the study center; (6) discharge from rehabilitation unit to home environment; (7) no terminal disease/no delirium; (8) German-speaking; and (9) written informed consent from participant or care giver. All patients admitted to the geriatric inpatient rehabilitation at the AGAPLESION Bethanien Hospital are consecutively screened for inclusion.

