### Motor performance

Key motor performances will be assessed using the Short-Physical-Performance-Battery (SPPB) including sub-tests of static balance, walking performance and sit-to-stand performance [33]. Outcome parameters are the total SPPB score (i.e. 0–12 scores) calculated as the summation of each sub-test score and the scores in each of the sub-tests (i.e. 0–4 scores) [33]. The “Timed Up and Go-test” (TuG) is performed to assess basic functional mobility [34]. Outcome parameter is the time in seconds needed to perform the task.

Additionally, objective performance measures are registered for SPPB using advanced body-fixed motion sensors (DynaPort MT, McRoberts B.V., The Hague, Netherlands). The sensor is attached to subject’s lower back at the height of the second lumbar vertebra. The measurement system (106.6 × 58 × 11.5 mm, 55 g) contains three pre-calibrated seismic accelerometers (sensor range: ± 2 g, resolution: 1 mg) and three gyroscopes (range: ± 100 deg./s, resolution: 0.0069 deg./s). Data is recorded at a sampling rate of 100 Hz. Outcome parameters are defined as body sway in terms of Center of Pressure (CoP) displacements in mm and CoP velocity in mm/s to evaluate static balance performance. During the 5-times-chair-rise test, sit-to-stand and stand-to-sit durations in seconds and maximum angular velocities in deg./s are calculated.

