### Statistical analysis and sample size

An intention to treat analysis will be conducted. We performed an a priori power analysis to determine the sample size necessary to obtain significant effects in PA. Power analysis for PA is difficult to calculate since studies using identical sensor-based physical activity assessments in cognitively-impaired geriatric patients have not been available. Thus, the effect size is based on a study conducting a functional strength training program in 137 institutionalized patients [54]. PA, as assessed by the MTI Actigraph, showed an average increase of PA by 43% in the strength training group compared to a control group (effect size: eta^2^ = 0.18). A priori power analysis was performed using GPower 3.1 software [55]. A repeated measure analysis of co-variance (ANCOVA) design including two groups and two repeated measurements yielded a total sample size of *N* = 101 (α = 0.05; critical F = 2.69). Estimating a drop out of 15%, we will recruit a total of 116 participants. For motor performance, as assessed by the SPPB total score, a pilot study conducted by our research group showed that performance improvements can be achieved using relatively small sample sizes (*N* = 34; large effect size: eta^2^ = 0.22 [56]). Repeated measures ANCOVA will be used to determine effects of the home-based training program on primary and secondary outcomes for effects of intervention (T1-T2) and sustainability of effects (T1-T3). Effect sizes are determined by calculating eta^2^ [57]. All data will be analyzed using SPSS 23.0 (SPSS Inc., Chicago, Ill., USA).

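### The walk is the only SPPB component with no named continuous outcome; adding gait speed or walk time would recover power at little cost

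*Protocol article*

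**What the plan says.** Under Motor performance, the SPPB is described as "including sub-tests of static balance, walking performance and sit-to-stand performance". Its outcome parameters are the total score and "the scores in each of the sub-tests (i.e. 0–4 scores". Secondary outcomes repeats this as "SPPB sub-test scores (0–4 points each". Neither section names a walking time or gait speed.

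The same Motor performance section adds sensor measures taken during the SPPB:

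- Balance: centre-of-pressure displacement and "CoP velocity in mm/s to evaluate static balance performance".
- Chair rise: "During the 5-times-chair-rise test, sit-to-stand and stand-to-sit durations in seconds and maximum angular velocities in deg./s are calculated".
- Walk: nothing named.

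Two other sources touch on walking. TuG is a test of basic functional mobility: "Outcome parameter is the time in seconds needed to perform the task". The gait parameters (cadence, steps, step duration, regularity, turning velocity) come from activity monitors worn for 48 h, according to Physical activity.

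On analysis, Statistical analysis and sample size states: "Repeated measures ANCOVA will be used to determine effects of the home-based training program on primary and secondary outcomes".

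**The concern.** A 0-4 score groups an underlying walking performance into a few bands. A patient who walks faster at T2 but stays in the same band counts as unchanged. A banded T1 score is also a weaker covariate than the measured T1 value, so the baseline adjustment loses precision as well.

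Walking matters to this trial. The Intervention section directs exercises at dynamic postural control, including walking. The Background criticises earlier trials for not taking gait, balance and strength as primary endpoints. Yet gait is the one of these three without a named continuous SPPB measure. At stake is a secondary result: the trial could report no effect on the walking sub-test although the walk itself improved.

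**Working it through.** The article states no figure on this point, so there is nothing to reproduce. Everything below on speeds, cut-points, effect and non-walkers is assumed; only the sample size comes from the article.

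**Sample.** 116 recruited less 15% drop-out: 116 × 0.85 = 98.6, taken as 49 vs 50.

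**1. Cost of banding a single measurement.** For a normal measurement cut at points c and given equally spaced integer scores, efficiency relative to the measurement is (Σφ(c))² / Var(score). For four equal bands the cuts are −0.674, 0 and 0.674 SD:

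- Σφ = 0.318 + 0.399 + 0.318 = 1.035
- Var(0, 1, 2, 3 with equal weight) = 1.25
- Efficiency = 1.035² / 1.25 = 0.86

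Other band shares, with power for 50.5 per arm at an assumed effect of 0.5 SD (0.71 if not banded):

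| Band shares | Efficiency | Power |
|---|---|---|
| 15/35/35/15% | 0.88 | 0.66 |
| Four equal bands | 0.86 | 0.64 |
| Half in the top band | 0.78 | 0.60 |
| 60% in the bottom band | 0.72 | 0.57 |
| 70% in the top band | 0.62 | 0.51 |
| 85% in the top band | 0.42 | 0.37 |

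The loss is about 12-14% of the information if patients spread over the bands, and larger if they pile up in one. This leaves out the weaker T1 adjustment.

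**2. Banding at T1 and follow-up, everyone able to walk.** Assumptions: mean speed 0.35-0.65 m/s, SD 0.20, T1-T2 correlation 0.6 or 0.75, true gain 0.08 m/s, cut-points 0.46/0.65/0.83 or 0.43/0.60/0.77 m/s, linear model adjusted for the T1 value.

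Power with speed can be checked by hand. The residual SD is 0.20 × √(1 − ρ²), and √(1/49 + 1/50) = 0.201.

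- ρ = 0.75: residual SD 0.132; 0.08 / (0.132 × 0.201) = 3.01; power ≈ Φ(3.01 − 1.98) ≈ 85%.
- ρ = 0.6: residual SD 0.16; 0.08 / (0.16 × 0.201) = 2.49; power ≈ Φ(2.49 − 1.98) ≈ 69%.

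Simulation agrees: about 68-85% with speed against 44-71% with the score, a loss of about 11-31 points. The loss is present without floor clustering. At mean 0.65 and ρ = 0.75 the bands hold about 17/33/32/18% of patients, and power still falls from 84% to 71%.

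**3. Patients unable to walk at follow-up.** Same model, ρ = 0.75, cut-points 0.46/0.65/0.83, with an assumed equal share of non-walkers in both arms. Power in %:

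| Mean speed (m/s) | Non-walkers | Speed, 0 m/s entered, linear | 0-4 score | Speed, non-walkers ranked lowest, rank ANCOVA |
|---|---|---|---|---|
| 0.35 | 0% | 83 | 52 | 80 |
| 0.35 | 5% | 64 | 40 | 62 |
| 0.35 | 10% | 49 | 29 | 50 |
| 0.55 | 0% | 84 | 71 | 80 |
| 0.55 | 5% | 55 | 50 | 62 |
| 0.55 | 10% | 38 | 37 | 48 |
| 0.65 | 0% | 84 | 71 | 79 |
| 0.65 | 5% | 46 | 45 | 62 |
| 0.65 | 10% | 31 | 33 | 49 |

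The last column is a separate run of 4,000 replicates with the same settings. Simulation error is about 1 point per cell, so gaps of 1-2 points mean nothing. Entering 0 m/s in a linear model removes most or all of the gain at the two higher mean speeds, because a few zeros inflate the residual variance. The rank analysis beats the score in every row. With no non-walkers it gives up about 3-5 points against the linear model on speed.

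**The case against.** The strongest reply is that walking under test conditions is not measured by a category alone. TuG time is continuous and stands in the same outcome line. The list of sensor measures under Secondary outcomes is introduced as examples, and a condensed article may leave a walking parameter unnamed. Walking in daily life is covered by the primary activity outcome, steps, cadence and GPS distances. Analysing the sub-tests as scores is a legitimate choice.

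Much of this stands. A reader might infer that the plan has no continuous test-based mobility result at all; TuG contradicts that. What remains is narrower. TuG is a composite and cannot show whether the walk changed. The examples only repeat measures that Motor performance defines for balance and chair rise. Daily-life activity describes what patients do, not how they perform the test.

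Some further inferences are tempting but not in the article:

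- That these patients cluster in the lowest bands: no speeds or cut-points are given.
- That banding is like discarding 30-50% of patients: this depends on the assumed distribution, and it fails if non-walkers are entered as 0 m/s in a linear model.
- That every patient has a T1 speed: the criterion "ability to walk 4 m without support" governs inclusion of patients screened on the ward, whereas T1 is measured later, at home.
- That the walk is timed: this is standard for the instrument but not stated.

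**Conclusion.** The point holds as a minor improvement to a secondary outcome. The SPPB walk is the only component without a named continuous measure, and analysing it as a 0-4 score costs power. If all patients can walk, the loss is about 11-31 percentage points under the assumed speeds, cut-points, correlations and 0.08 m/s gain; the true size cannot be told from the article. The gain from using speed survives a modest share of non-walkers only if the analysis handles them suitably. Nothing in the plan is stated wrongly or contradicted, and the primary SPPB total is unaffected. A reader might take this as a flaw in the main motor result; the documents do not support that.

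**What to change.** In Motor performance and Secondary outcomes, add gait speed (m/s), or walk time, from the same SPPB walk as the main analysed secondary outcome for walking, adjusted for its T1 value. State that patients unable to walk at T2 or T3 are ranked lowest and that the comparison is a rank-based ANCOVA, not a linear model with 0 m/s entered. Keep the 0-4 walking score for building the SPPB total and for description.

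The cost is about one line in each section, with no new test or visit. The walk time must be recorded and kept. The three sub-test results will no longer all be on one scale. A rank-based test gives no effect in m/s, so the group difference in speed has to be reported descriptively beside it.
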